## Abstract

**Introduction:**

Risk scoring is an integral part of the prevention of cardiovascular disease (CVD) and should form the basis for the decision to offer medication to reduce cholesterol (statins). However, there is a suggestion in the literature that many patients are still initiated on statins based on raised cholesterol rather than a raised CVD risk. It is important, therefore, to investigate the role that lipid levels and CVD risks have in the decision to prescribe. This research will establish how cholesterol levels and CVD risk independently influence the prescribing of statins for the primary prevention of CVD in primary care.

**Methods and analysis:**

The Health Improvement Network (THIN) is a database of coded primary care electronic patient records from over 500 UK general practices. From this resource, a historical cohort will be created of patients without a diagnosis of CVD, not currently receiving a prescription for statins and who had a lipid profile measured. A post hoc QRISK2 score will be calculated for these patients and they will be followed up for 60 days to establish whether they were subsequently prescribed a statin. Primary analysis will consist of predictive modelling using multivariate logistic regression with potential predictors including cholesterol level, calculated QRISK2 score, sociodemographic characteristic and comorbidities. Descriptive statistics will be used to identify trends in prescribing and further secondary analysis will explore what other factors may have influenced the prescribing of statins and the degree of interprescriber variability.

**Ethics and dissemination:**

The THIN Data Collection Scheme was approved by the South-East Multicentre Research Ethics Committee in 2003. Individual studies using THIN require Scientific Review Committee approval. The original protocol for this study and a subsequent amendment have been approved (16THIN009A1). The results will be published in a peer review journal and presented at national and international conferences.

Strengths and limitations of this studyThe use of a large, validated and generalisable set of general practices gives an unparalleled insight into current real-life medical practice.The use of a large cohort will allow the impact of lipid profiles and cardiovascular disease risk estimation to be modelled in an insightful and novel way.Insight into the decision to prescribe statins is limited to information that is coded in the electronic patient record and therefore much of the decision-making process will remain unknown.Recording of data may be incomplete and therefore some approximations will have to be made.

## Introduction

Predicted risk of cardiovascular disease (CVD) is determined from a combination of age, sex and cardiovascular risk factors.^1^
^2^ Risk of CVD is the best predictor of the benefits of statins because statins have the same proportional effect on people at low and high risk.^3^ Because of this, assessment of predicted risk of CVD has been a fundamental part of national clinical guidance on CVD prevention in primary care since 1998.^4^ In the UK, an absolute risk of CVD greater than a threshold was, and remains, a criterion for offering statin treatment and, in combination with raised blood pressure, a criterion for antihypertensive treatment.^5–7^ Risk assessment is also embedded in clinical guidelines around the world including New Zealand, Europe and America.^8–10^ A variety of different risk calculators are available and while QRISK2^11^ is the calculator of choice in England and Wales, elsewhere, others such as Framingham,^1^ Score,^12^ ASSIGN^13^ or Procam^14^ are recommended.

Statins are the only class of lipid-lowering medications recommended for use in UK primary care^5^ and are the most widely prescribed medication in England.^15^ A small proportion of patients in England have to pay a prescription charge for their medications but the majority receive their medication free.^16^ Statins are used to lower lipids as part of a CVD primary prevention strategy. As estimated CVD risk is the best predictor of likely benefits of treatment this information is necessary for effective shared decision-making when considering the use of statins.^17^ Evidence suggests that usage of risk scoring improves accuracy of perceived CVD risk and medical prescribing without causing harms.^18–20^

In the context of primary prevention, there is evidence both of undertreatment of high-risk patients (above the treatment threshold) and inappropriate treatment of low-risk patients (below the treatment threshold).^21–24^ Moreover, patients with the highest absolute CVD risk are at greatest risk of being undertreated.^25^ One reason for this is that risk scores may not be consistently used by clinicians to guide decision-making.^26^ Reasons for not using risk score calculators include a belief that risk scoring oversimplifies the decision and may lead to overprescribing^27^ and confusion over how best to use risk score calculators.^28^

Additionally, one fundamental barrier to using risk scores is a focus on individual risk factors over absolute risk score.^22^
^29^ It may appear logical that decisions about initiating cholesterol-lowering medication should be based on the patient's cholesterol level, and indeed this was the preferred approach in the pre-CVD risk era.^30^
^31^ However, this approach would not necessarily result in the greatest benefits and is not justifiable based on the available evidence. Despite this, there is evidence that this approach prevails in some areas. After adjusting for other CVD risk factors, lipid profile has been found to predict statin initiation in a US study^32^ and a randomised theoretical experiment in Australia highlighted clinicians’ preferences for managing individual risk factors over absolute risk.^33^ To further compound the problem, patients find it difficult to make decisions based on future risks and tend to preferentially focus on cholesterol levels when considering taking statins.^34^
^35^

In 2014, guidelines for England and Wales on lipid modification reduced the predicted risk threshold at which patients should be offered statins from a 20% 10-year risk to 10%.^5^
^7^ This recommendation was met with considerable concern from the medical community that it would lead to widespread overprescribing of statins with little clinical benefit but considerable potential for harm.^36^
^37^ This widely publicised criticism may have increased concerns that risk scoring leads to oversimplification of clinical decisions and overprescribing and may have, perversely, decreased the use of risk scoring and reinforced the use of lipid levels to guide decision-making. There is some evidence to suggest there was a decrease in statin initiations around this time due to the negative media attention.^38^

This research will investigate the relationship between lipid profile, QRISK2 score and subsequent initiation of statins by primary care clinicians. This will give an indication of the patient factors that are influencing the decisions clinicians make in routine practice when considering the use of statins and how this has changed in response to external factors.

The consistent use of risk scoring can result in more targeted prescribing and fewer patients being prescribed medication overall^39^ which maximises the efficiency and cost-effectiveness of treatment at a population level.

## Aims and objectives

*Aim*: To establish whether UK primary care patients are initiated on statins based more on their lipid levels or on their predicted CVD risk and if this has changed over time.

*Objectives*:

For primary prevention of CVD
To evaluate how lipid levels and CVD risk independently predict subsequent prescribing of statins.To determine if the relationship between lipid levels, QRISK2 score and statin prescribing has changed following recent guideline changes.To investigate the contribution that calculating a QRISK2 score has on the probability of initiating statin therapy.To investigate interprescriber variation when initiating statins.

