Immunosuppressant medication	Yes, no
Year quartile	1st, 2nd, 3rd, 4th

*Schizophrenia, bipolar affective disorder, mania or psychosis (unspecified), psychotic depression.

†Systemic lupus erythematosus, scleroderma, Bechet's syndrome, other inflammatory arthritis.

BMI, body mass index; BP, blood pressure; CVD, cardiovascular disease; HDL, high-density lipoprotein.

The potential cohort size can be estimated from the literature. Feasibility data from the THIN database identified over 360 000 patients over 2 years who were eligible for statin treatment for the primary prevention of CVD and had a lipid result and blood pressure coded on their medical record.^22^ Over a 5-year period we should expect to identify over double this number. Another cohort identified just over two million patients in the THIN database in the age range where NHS health checks are offered.^48^ Given that every patient who attends an NHS health check should have a lipid test undertaken and 20% of 40–75 years old are invited to have a health check each year, with ∼50% taking up this offer.^49^ This would generate around 200 000 coded lipid results in the target population annually.

The accuracy of the post hoc QRISK2 calculations will be tested through comparisons with corresponding coded QRISK2 scores in patients where these are available.

Additional modelling will also be undertaken to consider whether having a QRISK2 score coded on the medical record affects the probability of having a statin prescribed after adjustment for the level of CVD risk. Secondary analysis will also establish whether the threshold for initiating statins has changed over the course of the study period. The mean lipid levels and QRISK2 scores (both coded and calculated post hoc) of those initiated on statins and those not initiated on statins will be calculated each year to reveal any trends in the thresholds for initiation.

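### The yearly mean QRISK2 of initiators, part of the stated measure of change for Objective 2, can fall both when clinicians adopt the lower 2014 threshold and when they retreat from risk scoring

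*Protocol article*

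**What the plan says.** The second objective (Protocol article, Aims and objectives) is "To determine if the relationship between lipid levels, QRISK2 score and statin prescribing has changed following recent guideline changes". The Introduction says the study will show which patient factors influence prescribing decisions and "how this has changed in response to external factors".

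The same Introduction describes two influences close together in time. In 2014 the guideline for England and Wales lowered the predicted risk at which statins should be offered from 20% to 10%. The recommendation then met published criticism, which "may have, perversely, decreased the use of risk scoring and reinforced the use of lipid levels to guide decision-making". It continues: "There is some evidence to suggest there was a decrease in statin initiations around this time due to the negative media attention".

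For change over time, the Analysis section says that mean lipid levels and mean QRISK2 scores, in patients who were and were not started on a statin, "will be calculated each year to reveal any trends in the thresholds for initiation". Table 1 has a term for quarter of the year, added for seasonality, and none for calendar year or period. The prescriber analysis compares 2012–2013 with 2015–2016. Potential limitations does not mention that the guideline and the criticism coincided.

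**The concern.** The two influences predict different prescribing. Adopting the lower threshold means more initiation at 10–19.9% predicted risk. Retreating from risk scoring means a flatter relation of initiation to QRISK2 and a steeper relation to cholesterol. Objective 2 and the aim (lipid levels or risk, and whether this changed) depend on telling these patterns apart.

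A mean among initiators compresses the risk gradient into one number, and both patterns can lower it. If it falls after 2014, the natural reading, given that the plan calls it a trend in the threshold for initiation, is that clinicians now treat at lower risk as the guideline asked. The same fall could mean that they rely less on risk. The conclusion on Objective 2 could then be the reverse of what happened.

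**Working it through.** **No figure in the plan applies directly.** The article gives no expected prescribing rates by risk band, so everything numerical below is an illustration with assumed inputs.

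**Direction.** Under uptake alone, extra initiators come from the 10–19.9% band. Their mean score is below 20, so initiators' mean falls whenever it starts above the mean score of those added. Under retreat, the gradient of initiation across bands flattens, initiators are drawn more from lower bands, and the mean falls again.

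**Assumed inputs.**
- QRISK2 lognormal, median 8%, log-SD 0.8. Total cholesterol (TC) mean 5.5, SD 1.0 mmol/L, independent of QRISK2.
- Before: base initiation 2, 6, 8 and 20% in the article's four QRISK2 bands (<10, 10–14.9, 15–19.9, ≥20%), multiplied by 1, 1.5 and 3 in its three TC bands.
- Uptake: 2, 4 or 6 percentage points added to the base rate in the two middle bands.
- Retreat: each base rate r becomes r^e × 0.02^(1−e), with e = 0.9, 0.8 or 0.7. This holds <10% at 2% and pulls the others towards it. All rates are then multiplied by 0.776 (a general fall of about 22%), and the TC multipliers become 1, 1.7 and 4.

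**Results.** Relative change is the before/after odds ratio at 10–19.9% divided by that in the comparator band.

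| Scenario | Initiators' mean QRISK2 | Initiators' mean TC | Initiation ratio, 10–19.9% to <10% | Relative change vs <10% | Relative change vs ≥20% |
|---|---|---|---|---|---|
| Before | 20.1 | 5.76 | 3.34 | – | – |
| Uptake, +2 points | 19.6 | 5.76 | 4.34 | 1.34 | 1.34 |
| Uptake, +4 points | 19.1 | 5.76 | 5.34 | 1.71 | 1.71 |
| Uptake, +6 points | 18.7 | 5.76 | 6.34 | 2.10 | 2.10 |
| Retreat, e = 0.9 | 19.1 | 5.84 | 2.96 | 0.87 | 1.22 |
| Retreat, e = 0.8 | 18.2 | 5.84 | 2.62 | 0.76 | 1.42 |
| Retreat, e = 0.7 | 17.1 | 5.84 | 2.32 | 0.67 | 1.63 |
| Both (+6, e = 0.8) | 17.4 | 5.84 | 4.38 | 1.34 | 2.50 |

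**Arithmetic for two rows.** Before, initiation is 2.89, 9.66 and 28.96% in <10, 10–19.9 and ≥20%.
- Uptake of +6 points: 10–19.9% becomes 18.34%. Odds ratio (0.1834/0.8166) ÷ (0.0966/0.9034) = 2.10. The other bands are unchanged, so both relative changes are 2.10.
- Retreat with e = 0.8: 2.54, 6.66 and 16.07%. Odds ratios 0.876, 0.668 and 0.470. Relative change 0.668/0.876 = 0.76 against <10%, and 0.668/0.470 = 1.42 against ≥20%.

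**Reading the table.** Uptake of +4 points and retreat with e = 0.9 give the same mean QRISK2, 19.1, from opposite behaviour. The ratio of 10–19.9% to <10% separates them: it rises with uptake (to 5.34) and falls with retreat (to 2.96). The contrast with ≥20% alone does not, because it rises in both. Both comparators are needed, together with the cholesterol gradient.

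**Model size.** A period term (1), its interaction with calculated QRISK2 (3) and with TC (2) add 6 degrees of freedom. Under the article's rule of 10 per degree of freedom, 57 + 6 = 63 needs 630 initiations instead of 570. The article expects around 200 000 lipid results a year, so size is no obstacle.

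**The case against.** **No guideline effect is claimed.** The aim asks whether things changed over time, and following can be read as purely temporal. The Introduction presents the criticism as a reaction to the recommendation, so the net change after 2014 is a legitimate answer. This stands: reporting net change is acceptable. But Objective 2 concerns the form of the relationship, and the planned mean can mislead about that form even when no cause is named.

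**The plan also reports mean lipids.** In the illustration, initiators' mean TC rises under retreat and not under uptake, so it carries some information. The rise is only 0.08 mmol/L, and the clean split depends on assuming TC independent of QRISK2. When both influences act, mean TC is the same as under retreat alone, so it cannot show whether uptake also occurred.

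**The article condenses a fuller plan.** An interaction term could be left to that plan. The point here is the measure that the article does name.

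**A reader might infer that the two influences cancel, so that a null hides a guideline effect.** That can happen to a crude prescribing rate: with +6 points and a uniform 22% fall, the overall rate is 7.96% before and after. It does not carry over to the planned means. In that same scenario initiators' mean QRISK2 is 18.7, exactly as with uptake alone. Nor is the yearly series a simple before/after comparison, and the prescriber analysis already leaves out 2014.

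**A reader might also infer that the 10–19.9% against ≥20% contrast isolates the guideline.** It does so only if publicity acted equally across bands. Take assumed odds multipliers of 1.25 for the guideline at 10–19.9% and 0.8 for publicity. If publicity acts everywhere, the ratio is (0.8 × 1.25)/0.8 = 1.25. If it acts only at 10–19.9%, the ratio is 0.8 × 1.25 = 1.00. The Introduction makes unequal action plausible, since the criticism was aimed at the lowered threshold.

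**Conclusion.** The point holds as one of interpretation and choice of measure. The article itself names a threshold cut and a roughly concurrent reaction that may have moved clinicians back to lipids, then measures change by yearly means that do not separate the two. Under the assumed inputs, initiators' mean QRISK2 falls from 20.1 to between 18.7 and 19.6 with uptake alone, and to between 17.1 and 19.1 with retreat alone. The ranges overlap. The initiation ratio of 10–19.9% to <10% moves from 3.34 in opposite directions: up to 4.34–6.34, or down to 2.32–2.96.

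The sizes depend on assumed rates. The direction needs only that initiators' mean starts above the mean score of the newly added patients, and that retreat flattens the risk gradient. The documents do not support saying that the planned analysis will yield a false null, or that any band contrast gives a pure guideline effect. The criticism is dated only as around the time of the guideline.

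**What to change.** 1. Add to the logistic model a period term (before/after the guideline) and its interactions with the calculated QRISK2 bands and the total cholesterol bands. Split 2014 at the guideline date or leave it out, as the prescriber analysis already does.
2. Report the change in odds of initiation at 10–19.9% against both <10% and ≥20%, with the change in the cholesterol gradient. Keep the yearly means as description.
3. Describe the overall change as the net effect of all events of the period. Call a band-specific relative change consistent with guideline uptake, and state that this reading assumes publicity acted similarly across bands.
4. Add a sentence on the coincidence to Potential limitations.

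Cost: about 6 degrees of freedom (60 more initiations under the article's own rule), no new data, and a more cautious conclusion on Objective 2.

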## Methods and analysis

### Study design

A historical open cohort study of patients who were eligible for statin therapy for the primary prevention of CVD.

### Data source

Data will be extracted from anonymised primary care records from practices in England and Wales who contribute to The Health Improvement Network (THIN) database. The THIN database contains routine patient data from over 500 UK general practices which are generalisable to the UK population.^40^ THIN has been used in previous studies to validate QRISK2 and it was shown that the discrimination statistics in THIN are as good as those for the original QRISK2 cohort.^41^
^42^ Practices that contribute to THIN use the Vision (In Practice Systems) electronic patient records system. Clinical data are coded using Read code clinical classification V.2^43^ and drug codes are used which correspond to the British National Formulary (BNF).^44^ The clinical codes used are available in online supplementary appendix I and the drug codes are available in online supplementary appendix II.

10.1136/bmjopen-2016-013120.supp1supplementary appendix I

10.1136/bmjopen-2016-013120.supp2supplementary appendix II

All data are anonymised and will be stored on secure severs at the University of Birmingham and accessed only through password-protected systems.

### Population

Patients will be eligible for inclusion if they are aged between 40 and 84 years inclusive (the age range recommended by the National Institute for Health and Care Excellence (NICE) for risk assessment^5^) with no previous diagnosis of CVD and at least one lipid result coded in the study period. The date of the first coded lipid result in the study period will be considered the index date. Patients must not have been prescribed a statin prior to the index date.

In order to maintain a stable cohort of practices, only THIN practices in which there are data available for the whole study period will be included. The study period will run from the beginning of 2012 to the end of 2016. Patients will be eligible for inclusion from the earliest of the following dates: study start date, acceptable mortality reporting date (which ensures that patient deaths and deregistrations are being recorded consistently^45^), Vision date plus 1 year, registration date plus 1 year (to ensure time for baseline data to be recorded), and age 40; until the earliest of the following dates: age 85, study end date, CVD diagnosis, other excluding diagnosis (as below), statin initiation or recording of a contraindication for the prescribing of statins. Patients will also be excluded if they left the database within 60 days of the index date.

Patients will be excluded if they had pre-existing CVD, were pregnant, had a contraindication to statin therapy (including allergies and drug interactions), were already being prescribed a statin (or other lipid-lowering therapy) or had ever been prescribed a statin in the past. Patients will be considered to have pre-existing CVD if they had a diagnosis of myocardial infarction, angina, peripheral vascular disease or stroke/transient ischaemic attack. Patients with type 1 diabetes mellitus, a diagnosis of chronic kidney disease stages 3–5 and patients diagnosed with or who were at risk of familial hypercholesterolaemia will also be excluded as statin use in these patients should not be based on CVD risk assessment. Patients at risk of familial hypercholesterolaemia will be defined as those with a total cholesterol of ≥9.0 mmol/L as this is the threshold for seeking specialist assessment defined in the NICE guidance.^5^

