## Study variables

### Exposure variables

The exposure of interest is the undertaking of lipid testing. Once a patient has their lipids recorded, this signifies that a clinician has made a decision about the significance of the lipid levels and will act on this. Individual patients may have multiple lipid results recorded over the study period. Assuming the exclusion criteria are not met, each lipid result will be considered as a new exposure so long as it is not within 60 days of the last recorded lipid level. The number of previous lipid results will be included in predictive modelling.

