### Outcome variables

The outcome will be the prescription of a statin within 60 days of a set of lipid results.

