### Missing data and extreme values

Missing data are anticipated in some variables; notably BMI, blood pressure and smoking status. If comorbidities are missing they will be assumed to be absent. Missing values arise twice: first when calculating the QRISK2 score post hoc, and second when constructing the multivariable model. These citations will be accounted for differently.

Where data are missing from variables used in QRISK2 calculations, the imputed values used by the QRISK2 calculator will be used.^46^ In the multivariable model, all variables will be categorical and a ‘missing’ category will be used to account for the possibility that missing data are associated with the initiation of statins. Biologically implausible values for blood pressure, lipids, liver transaminases, height and weight will be identified and excluded.

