## Analysis

Continuous variables will be categorised. Calculated and coded QRISK2 scores will be categorised according to risk bands (<10%, 10–14.9%, 15–19.9% and ≥20%). Age will be categorised into four groups (40–49, 50–59, 60–69 and ≥70). Total cholesterol (TC) will be categorised into three bands (<5.0, 5.0–6.9 and ≥7.0 mmol/L), and high-density lipoprotein (HDL) cholesterol into four bands (≤1.2, 1.3–1.4, 1.5–1.7 and ≥1.8 mmol/L) as these cut-offs have been used previously in the literature.^22^ Systolic blood pressure will be split into three groups corresponding to normotensive, stage 1 hypertension and stage 2 hypertension (<140, 140–159 and ≥160 mm Hg).^6^

The cohort will be described and prescribing rates and QRISK2 score trends will be established.

The primary analysis will consist of predictive modelling using multivariate logistic regression (variables summarised in table 1). Clustering of responses within individual general practitioner (GP) practices will be included in the model. Variation throughout the year due to the seasonality imposed by the Quality and Outcomes Framework (QOF) targets will be accounted for by adding the year quarter as a variable in the model. Assuming a minimum sample size for analysis of 10 per degree of freedom,^47^ and 57 degrees of freedom in the variables, a minimum sample of 570 patients with a lipid profile and subsequent statin initiation should easily be obtained.

**Table 1 BMJOPEN2016013120TB1:** Variables used in predictive modelling

Variable	Categories
Total cholesterol	<5.0, 5.0–6.9, ≥7.0
TC/HDL ratio	≤1.2, 1.3–1.4, 1.5–1.7, ≥1.8
Prior cholesterol measurements	0, 1–2, 3–4, ≥5
Calculated QRISK2	<10%, 10–14.9%, 15–19.9%, ≥20%
Coded QRISK2	<10%, 10–14.9%, 15–19.9%, ≥20%, missing
Systolic BP	<140, 140–159, ≥160, missing
Age	40–49, 50–59, 60–69, ≥70
Sex	Male, female
Ethnicity	White, Asian, black, other, missing
Townsend deprivation quintile	1st, 2nd, 3rd, 4th, 5th, missing
Urban/rural score	Urban, rural, missing
BMI	<20, 20–24.9, 25–29.9, 30–34.9, 35+, missing
Smoking status	Current smoker, ex-smoker, non-smoker, missing
Liver transaminases	Normal, abnormal, missing
Diabetes mellitus	Yes, no
Family history of CVD	Yes, no
Atrial fibrillation	Yes, no
Rheumatoid arthritis	Yes, no
Hypertension	Yes, no
Chronic kidney disease	Yes, no
HIV	Yes, no
Severe enduring mental illness*	Yes, no
Inflammatory conditions†	Yes, no
Antipsychotic medication	Yes, no
Long-term corticosteroids	Yes, no

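### The qualifying test is any coded lipid result, and the modelled lipid value need not come from that test, so an older or later value can stand in for the result the clinician acted on

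*Protocol article*

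**What the plan says.** All references are to the protocol article.

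- **Eligibility and index date (Population).** A patient needs "no previous diagnosis of CVD and at least one lipid result coded in the study period", and "The date of the first coded lipid result in the study period will be considered the index date".
- **Exposure (Exposure variables).** Subject to the exclusions and a 60-day spacing, "each lipid result will be considered as a new exposure". The rationale is that a recorded lipid result marks a clinician's judgement on it.
- **Other wording for the same event.** The abstract describes patients "not currently receiving a prescription for statins and who had a lipid profile measured". Outcome variables says "The outcome will be the prescription of a statin within 60 days of a set of lipid results". The sample-size text in Analysis also refers to a lipid profile.
- **Date of the predictor values (Predictor variables).** With a coded QRISK2 score on the index date or in follow-up, the latest data up to the coding date are used. Without one, the latest data up to day 60 are used. No earliest date is set, and lipids are not treated separately.
- **Missing data (Missing data and extreme values).** For the post hoc score: "Where data are missing from variables used in QRISK2 calculations, the imputed values used by the QRISK2 calculator will be used". For the multivariable model, a missing category is promised. Implausible lipid values are removed.
- **Table 1.** The total cholesterol row reads "Total cholesterol <5.0, 5.0–6.9, ≥7.0". The TC/HDL row has four bands. Neither has a missing level. The Analysis text applies the same four bands to HDL itself.
- **Codes (Data source).** "The clinical codes used are available in online supplementary appendix I"; that appendix was not available for this review.

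**The concern.** The exposure rests on the idea that the clinician has just seen and judged a particular lipid result. The aim is to learn whether that lipid level or the predicted risk drives prescribing. Both predictors should therefore carry the information available at that decision. The eligibility and exposure rules do not ensure that the qualifying test supplies it, and the dating rule does not require the modelled value to come from that test.

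An older value misstates what the clinician saw. A later value may postdate the prescription and, since the Introduction says statins are used to lower lipids, may already reflect treatment. An imputed lipid input removes that patient's own lipid information from calculated QRISK2. These errors fall on the two predictors being compared. Total cholesterol from the test also matters elsewhere: for the familial hypercholesterolaemia exclusion (Population) and for the split at 6.5 mmol/L in the prescriber score (end of Analysis).

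**Working it through.** **1. What each lipid variable needs.**
- Total cholesterol predictor: total cholesterol only.
- Second predictor: HDL and total cholesterol if it is the TC/HDL ratio (Table 1), or HDL alone if it is HDL (Analysis text). Either way, HDL is needed unless a ratio is coded.
- QRISK2: Predictor variables lists only lipids, without components.

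**2. Follow one test through the rules.** Take a total cholesterol recorded without HDL.
- It is a coded lipid result, so under Population and Exposure variables it opens an exposure, unless the appendix code list prevents this.
- If an HDL was recorded earlier, the dating rule uses it, however old it is.
- If an HDL is recorded later, up to the coded QRISK2 date or day 60, the rule uses that value instead, even if a statin has already been prescribed. A full profile within 60 days of the first result does not open its own exposure, so it feeds the exposure opened by the partial test.
- If there is no HDL at all, the missing-data section assigns a missing category, but Table 1 has no such level for the HDL-based variable. If calculated QRISK2 then lacks a lipid input, the calculator's imputed value is used.

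Carry-forward and imputation are alternatives: imputation applies only where no value exists.

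The later-value route does not need an incomplete test. A complete qualifying profile followed by a repeat profile on day 50 would be modelled with the day-50 values if no QRISK2 score is coded. Removal of an implausible component can also leave a full profile incomplete.

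**3. The plan's own sample-size figure.** 10 per degree of freedom × 57 = 570, as stated. Counting levels minus one over the 27 variables of Table 1:
- 15 multi-level or sex variables: 2 + 3 + 3 + 3 + 4 + 3 + 3 + 1 + 4 + 5 + 2 + 5 + 3 + 2 + 3 = 46
- 12 yes/no variables: 12
- Total: 58, so a minimum of 580, within 2% of 570.

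Adding a missing level to both lipid variables gives 60 degrees of freedom and 600. Adding it to the HDL-based variable alone gives 59 and 590.

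**4. Scale.** The article expects over double 360 000 patients: 2 × 360 000 = 720 000. The share of qualifying tests lacking a component is not given. The shares below are assumptions, for illustration only.

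| Assumed share | Patients affected | Patients left if dropped |
|---|---|---|
| 1% | 7 200 | 712 800 |
| 5% | 36 000 | 684 000 |
| 10% | 72 000 | 648 000 |
| 20% | 144 000 | 576 000 |
| 30% | 216 000 | 504 000 |

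Even at 30%, reaching 570 initiations needs an initiation proportion of only 570 / 504 000 = 0.11%.

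**The case against.** The strongest reply is that lipid result is shorthand for lipid profile. Three other places say profile or set, the missing-data section does not name lipids among the variables expected to be incomplete, and Table 1 may omit a missing level because the authors expect every qualifying test to be complete. The code list in appendix I may also restrict what counts. This is a fair reading of intent, and it limits the point about incomplete tests. It does not dispose of the dating rule. A code list does not by itself require two components on the same date, and nothing in it would stop the rule from replacing the qualifying value with a later one.

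Several stronger readings are tempting, but the documents do not support them:
- A reader might infer that every lipid predictor and QRISK2 need both total cholesterol and HDL. The total cholesterol predictor does not, and the QRISK2 components are not named.
- A reader might infer that a lone triglyceride or LDL opens an exposure. The article mentions neither, and the answer lies in the appendix.
- A reader might infer that incomplete tests cannot enter the model. The missing-data section provides a category for them; the fault is that Table 1 does not show it.

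A further fair objection is that restricting the cohort to full profiles may select consultations that were formal risk assessments, which bears on the contrast under study. That stands as a cost of the fix.

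**Conclusion.** The point holds as a matter of exposure definition and dating. The eligibility and exposure rules use looser wording than the abstract, the outcome and the sample-size text. Table 1 and the missing-data section disagree about a missing level for lipids. Most importantly, the stated dating rule allows the modelled lipid value to be older or later than the result that defines the exposure, including one recorded after the statin decision.

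The size of the resulting bias cannot be derived: the documents give neither the share of incomplete tests nor the share of exposures with a further lipid result before the cut-off. The counts in the table rest on assumed shares and should not be read as estimates. That incomplete tests differ systematically from full profiles is plausible but not documented. The minimum of 570 initiations is not at risk under any share considered. The change is worth making because it is cheap and protects the main comparison.

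**What to change.** 1. In Population and Exposure variables, define a qualifying exposure as a same-date set with plausible values for total cholesterol and HDL (or a coded TC/HDL ratio), in line with the abstract. The index date becomes the date of the first such set.
2. In Predictor variables, take the modelled lipid values and the QRISK2 lipid input from that set. The latest-available rule would no longer apply to lipids. The check of calculated against coded QRISK2 could still use the value current at coding, since its purpose is to reproduce the recorded score.
3. Report how many tests the definition drops, and state whether dropped tests still count towards prior measurements and the 60-day spacing.
4. Add a sensitivity analysis that keeps tests with total cholesterol only, with an explicit missing level for the HDL-based variable, and align Table 1 with the missing-data section. By the count above this adds one degree of freedom (59, minimum 590).

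The cost is a few lines of text, an extraction filter and one extra model. Some tests are lost, and the primary results describe patients with a usable profile, possibly tilted towards formal risk assessments. The sensitivity analysis shows whether that matters.
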